## Abstract

**Introduction:**

Malignant peritoneal mesothelioma (MPM) is an uncommon but aggressive neoplasm and has a strong association with asbestos exposure. MPM has low survival rates of approximately 1 year even after (palliative) surgery and/or systemic chemotherapy. Recent advances in treatment strategies focusing on cytoreductive surgery (CRS) and hyperthermic intraperitoneal chemotherapy (HIPEC) have resulted in improved median survival of 53 months and a 5 year survival of 47%. However, recurrence rates are high. Current systemic chemotherapy in the adjuvant setting is of limited efficacy, while immunotherapy with dendritic cell based immunotherapy (DCBI) has yielded promising results in murine models with peritoneal mesothelioma and in patients with pleural mesothelioma.

**Methods and analysis:**

The MESOPEC trial is an open-label single centre phase II study. The study population are adult patients with histological/cytological confirmed diagnosis of epithelioid malignant peritoneal mesothelioma. Intervention: 4 to 6 weeks before CRS-HIPEC a leukapheresis is performed of which the monocytes are used for differentiation to dendritic cells (DCs). Autologous DCs pulsed with allogeneic tumour associated antigens (MesoPher) are re-injected 8 to 10 weeks after surgery, three times biweekly. Additional booster vaccinations are given at 3 and 6 months.

Primary objective is to determine the feasibility of administering DCBI after CRS-HIPEC in patients with malignant peritoneal mesothelioma. Secondary objectives are to assess safety of DCBI in patients with peritoneal mesothelioma and determine whether a specific immunological response against the tumour occurs as a result of this adjuvant immunotherapy.

**Ethics and dissemination:**

Permission to carry out this study protocol has been granted by the Central Committee on Research Involving Human Subjects (CCMO in Dutch) and the Research Ethics Committee (METC in Dutch). The results of this trial will be submitted for publication in a peer-reviewed journal.

**Trial registration number:**

NTR7060. EudraCT: 2017-000897-12; Pre-Results.

Strengths and limitations of this studyThe dendritic cell vaccines used in this protocol can be manufactured on a large scale, because autologous dendritic cells are loaded with allogeneic tumour associated antigens.Dendritic cell based immunotherapy has shown to have very limited side effects, especially when compared with systemic chemotherapy.This study will provide clinicians and scientists with important information about the immunological response after dendritic cell vaccination.Since all patients undergo cytoreductive surgery and hyperthermic intraperitoneal chemotherapy prior to dendritic cell based immunotherapy (DCBI), the effect of DCBI must be determined by assessing the immune response and overall clinical condition of each patient.In this phase II clinical trial the effect of DCBI on disease-free and overall survival cannot be determined, when DCBI is considered safe and feasible, a phase III clinical trial will be conducted to determine the effect on survival.

## Introduction

Malignant peritoneal mesothelioma (MPM) is a highly lethal neoplasm, arising from the serosal lining of the peritoneal cavity. It has a strong association with exposure to asbestos. Non-specific clinical symptoms like weight loss, abdominal pain and distension contribute to a delay in diagnosis. As a result, the majority of MPM cases are identified at an advanced stage, creating an overall poor life-expectancy of 4 to 12 months if left untreated.^1^ Even after (palliative) surgery and/or systemic chemotherapy, MPM has poor survival of approximately 1 year.

In recent years treatment focus has shifted towards a more aggressive approach, utilising cytoreductive surgery (CRS) and hyperthermic intraperitoneal chemotherapy (HIPEC). Patients that underwent this treatment had a better prognosis with median survival of 53 months and 5 year survival of 47%.^2^ However, even after CRS-HIPEC, recurrence rates are high with reported median progression-free survival and disease-free survival ranging from 11 to 28 months and 7.2 to 40 months respectively.^1^ One explanation is that it is difficult to perform complete cytoreduction, as MPM often grows diffusely throughout the abdominal cavity,^3^ but even when macroscopic complete cytoreduction is reached, loco-regional recurrence is often seen. A study that included 108 patients in whom complete or near-complete cytoreduction was achieved showed local recurrence in 38% of patients after median follow-up of 48.8 months.^4^

Effective adjuvant therapies are pressingly needed for above mentioned reasons. Dendritic cell based immunotherapy (DCBI) has shown promising results by harnessing the potency and specificity of the immune system. The first DCBI for mesothelioma was developed in the Erasmus MC, Rotterdam, and has been tested in murine models with peritoneal mesothelioma and in clinical phase I/II studies for patients with pleural mesothelioma.^5–11^ These studies have shown that DCBI induces durable responses and higher survival rates compared with the general mesothelioma population. Dendritic cell (DC) therapy was well tolerated in these patients without grade 3 or 4 toxicities. Only low-grade fever and flu-like symptoms (grade 1 to 2) were seen for 24 hours after treatment. In a dose escalation phase I trial, the safety of using allogeneic tumour lysate (PheraLys) for the loading of the DCs was assessed. PheraLys is a tumour cell lysate derived from five well-characterised cell lines from patients with malignant mesothelioma. Tumour lysate priming strategies may be advantageous in providing the full antigenic repertoire of the tumour and might reduce the possibility of tumour escape by inducing a broader immune response. In this study adverse events were similar to earlier studies and importantly no severe adverse events were observed. Furthermore, clinical responses were established radiographically and some longtime survivors are being observed.

Previous preclinical studies demonstrated that DCBI has the capacity to slow down tumour growth, although tumour load has an important role in survival.^12^ Mice had a better outcome when DCs were injected early in tumour development.^5^ Mesothelioma cells produce specific cytokines and attract regulatory T-cells that suppress efficient immune responses, indicating that patients with low tumour load have a better functioning immune system and better anti-tumour responses.^13^ Therefore it is the aim of this trial to treat patients with DCBI after complete macroscopic cytoreduction and HIPEC. The residual disease after cytoreductive surgery is classified using the the ‘completeness of cytoreduction’ (CCR score). CCR-0 indicates no visible residual tumour and CCR-1 indicates residual tumour nodules ≤2.5 mm. CCR-2 indicates residual tumour nodules between 2.5 mm and 2.5 cm. CCR-3 indicates a residual tumour >2.5 cm. In this study CCR ≤1 is considered as complete macroscopic cytoreduction. However, when complete cytoreduction cannot be achieved during surgery, patients undergo palliative HIPEC followed by DCBI

Main objective of this clinical trial is to determine feasibility of administering adjuvant DCBI after CRS-HIPEC. Secondary objectives are to asses safety and determine if a specific immunological response against the tumour occurs after DC therapy. When DCBI is considered safe and feasible as adjuvant treatment for patients with MPM, further research (phase III study) is warranted to determine the effect on survival.

## Methods and analysis

### Study design

#### Trial setting

The MESOPEC trial is an open-label, single arm, single centre phase II clinical trial. This study is conducted in the Erasmus MC, Rotterdam, an academic hospital located in the Netherlands. All patients included in this trial will receive adjuvant DCBI after CRS-HIPEC. Trial registration details are described in table 1.

**Table 1 T1:** WHO trial registration data set

Primary registry and trial identifying number	EudraCT number: 2017-000897-12 Netherlands trial register: NTR7060
Date of registration in primary registry	October 2017
Protocol version	Protocol version 3.0, date 31-10-2017
SPIRIT guidelines data set for clinical trials	See online supplementary file
Source(s) of monetary or material support	Erasmus University Medical Centre, Rotterdam, the Netherlands Dutch Cancer Society (KWF Kankerbestrijding) Stichting Coolsingel
Primary sponsor	Erasmus University Medical Centre, Rotterdam, the Netherlands
Secondary sponsors	Dutch Cancer Society (KWF Kankerbestrijding) Stichting Coolsingel
Contact for public queries	[name], study coordinator Department of surgical oncology Erasmus MC, Rotterdam, the Netherlands [contact], [name] [name], study coordinator Department of surgical oncology Erasmus MC, Rotterdam, the Netherlands [contact], [name]
Contact for scientific queries	[name], principal investigator Department of surgical oncology Erasmus MC, Rotterdam, the Netherlands [contact], [name]
Public title	Adjuvant dendritic cell based immunotherapy (DCBI) after cytoreductive surgery (CRS) and hyperthermic intraperitoneal chemotherapy (HIPEC) for peritoneal mesothelioma: the MESOPEC trial
Scientific title	Adjuvant dendritic cell based immunotherapy (DCBI) after cytoreductive surgery (CRS) and hyperthermic intraperitoneal chemotherapy (HIPEC) for peritoneal mesothelioma: a phase II single centre open-label clinical trial
Countries of recruitment	The Netherlands
Health conditions or problems studied	Malignant peritoneal mesothelioma
Interventions	Vaccination with autologous dendritic cells loaded with allogeneic mesothelioma specific tumour antigens, after standard care (CRS-HIPEC)
Key inclusion and exclusion criteria	Inclusion criteria: Confirmed diagnosis of epithelial peritoneal mesothelioma WHO-ECOG performance status 0 to 1, expected survival at least 6 months Adequate organ function and bone marrow reserves Positive delayed type hypersensitivity skin test for positive control antigen Exclusion criteria: Extra-abdominal disease/metastatic disease Current use of steroids or other immunosuppressive agents Prior cytoreductive surgery Prior malignancy other than basal cell carcinoma within 10 years of inclusion Patients with a known allergy to shellfish Serious chronic or acute illness considered to constitute unwarranted high risk for CRS-HIPEC or dendritic cell treatment Pregnant or lactating women
Study type	Open label single centre phase II study
Date of first enrolment	March 2018
Target sample size	20
Recruitment status	Recruiting
Primary outcome	Feasibility (DCBI therapy is considered feasible when 75% of patients enrolled in this study are able to receive and finish dendritic cell vaccination after CRS-HIPEC)
Key secondary outcome(s)	Safety Immunological response after dendritic cell vaccination

CRS, cytoreductive surgery; ECOG, Eastern Cooperative Oncology Group; HIPEC, hyperthermic intraperitoneal chemotherapy; SPIRIT, Standard Protocol Items: Recommendations for Interventional Trials.

10.1136/bmjopen-2018-026779.supp1Supplementary file 1

#### Study population

The study population consists of adult patients diagnosed with MPM. Potentially eligible patients will be referred by their local clinician or through self-referral to a medical specialist and member of the study team to discuss the trial and determine eligibility.

In order to participate in the study, patients must meet the following inclusion criteria:Histologically or cytologically confirmed diagnosis of epithelioid MPM.WHO-Eastern Cooperative Oncology Group performance status of 0 or 1.Normal organ function and adequate bone marrow reserve (absolute neutrophil count >1.0×10^9^/l, platelet count >100×10^9^/l, haemoglobin >6.0 mmol/L).Positive delayed -type hypersensitivity skin test against at least one positive control antigen tetanus toxoid.Planned start date of vaccination within 8 to 10 weeks after CRS-HIPEC.Expected survival prior to surgery must be at least 6 months.At least 18 years of age, written informed consent according to International Council for Harmonisation-Good clinical practice (ICH-GCP), ability to return to the study centre for adequate follow-up.

A potential participant who meets any of the following criteria will be excluded from participation in the study:Extra-abdominal mesothelioma (ie, metastatic disease).Prior cytoreductive surgery.Prior malignancy other than basal cell carcinoma within 10 years of inclusion.Serious concomitant disease or infection, including HIV or chronic viral hepatitis.Current use of steroids or other immunosuppressive agents (at least 6 weeks discontinuation before the first vaccine, with exception of prophylactic usage of dexamethasone during chemotherapy).History of auto-immune disease or organ allografts.Any disease that is considered to constitute an unwarranted high risk for CRS-HIPEC by the surgeon or study coordinator.Pregnant or lactating women.

#### Patient timeline and additional procedures

Patients will undergo leukapheresis for dendritic cell vaccine production purposes 4 to 6 weeks before surgery. At baseline, subjects will undergo CRS-HIPEC.

At 6 weeks after surgery, the investigators will determine if the patient is sufficiently recovered and fit to undergo DCBI. Patients must have adequate bone marrow reserve before DCBI treatment; absolute neutrophil count >1.0×10^9^/l, platelet count >100×10^9^/l and haemoglobin >6.0 mmol/L.

Dendritic cell vaccinations will be given at 8 to 10 weeks after surgery three times biweekly. Before each vaccination laboratory testing will be performed and results reviewed before injection. Before and after injection vital signs (pulse, blood pressure, blood oxygen saturation and temperature) are determined. Patients are observed in the hospital for 2 hours after injection. Each vaccine contains at least 25×10^6^ cells. One-third of this is injected intradermal, two-thirds are administered intravenous. Intradermal injection will be performed in the left arm. Intravenous injection will be performed via the vena brachialis in the left arm through a basic peripheral venous catheter. After the third vaccination, delayed-type hypersensitivity (DTH) skin test is performed. When DTH skin test result is positive for the dendritic cell vaccine, a 3 mm skin biopsy will be taken for further analyses. At 3 and 6 months after the first vaccination, two additional booster vaccinations will be given. Additional to study-related treatment, patients receive standard care and follow-up required after CRS-HIPEC.

Total duration of the treatment protocol is 8 to 9 months. In total, 11 additional visits are required to adhere to the study protocol. For the production of DCBI patients undergo leukapheresis. For the purpose of immune-monitoring, additional blood samples will be collected at seven moments during the study. (figure 1)

**Figure 1 F1:**
[figure not shown]
Patient timeline: In total 11 additional visits are required. After informed consent is acquired, screening will take place in the form of full examination and DTH skin test. When patients comply to all criteria, they will undergo leukapheresis for production of dendritic cell vaccine. After 2 to 4 weeks patients undergo CRS-HIPEC. First vaccination is given 8 to 10 weeks after surgery, followed by two more vaccinations biweekly. DTH skin testing is performed for analysis of immune response 2 weeks after the third vaccination. At 3 and 6 months after first vaccination, subjects receive additional ‘booster’ vaccination. Each vaccine contains at least 25×10^6^ cells. One-third is injected intradermal. Two-thirds are administered intravenous. ANCA, anti-neutrophil cytoplasmic antibody; CRS, cytoreductive surgery; CT, computed tomography; DC, dendritic cell; DTH, delayed-type hypersensitivity; HIV, human immunodeficiency virus; HIPEC, hyperthermic intraperitoneal chemotherapy; MPM, malignant peritoneal mesothelioma; RBC, red blood cell; WBC, white blood cell.

#### Dendritic cell vaccine production

Dendritic cells are derived from peripheral blood mononuclear cells, by differentiating monocytes towards immature dendritic cells using specific cytokines. Immature dendritic cells are known for their high antigen uptake potential. Therefore they are exposed to tumour specific antigens in a co-culture with allogeneic mesothelioma cell lysate. This lysate (PheraLys) is derived from five well-specified mesothelioma cell lines. After exposure to PheraLys the immature dendritic cells are differentiated towards mature dendritic cells, which are ready to activate the immune system in vivo (MesoPher). (figure 2)

**Figure 2 F2:**
[figure not shown]
DCBI production process: Monocytes are isolated from peripheral blood and are then stimulated to differentiate towards immature dendritic cells. These immature dendritic cells are exposed to PheraLys tumour cell lysate. After further differentiation towards mature dendritic cells, MesoPher vaccinations are given back to the patient. DCBI, dendritic cell based immunotherapy.

#### Withdrawal of individual subjects

Subjects can leave the study at any time for any reason if they wish to do so without any consequences. The investigator can decide to withdraw a subject from the study for urgent medical reasons. Should a participant withdraw from the trial, then every effort will be made to obtain follow-up data, with the permission of the patient.

The investigators also have the right to withdraw patients from the study if one or more of the following events occur:Significant protocol violation or non-compliance on the part of the patient or investigator.Refusal of the patient to continue treatment or observations.Any change in the condition of the patient that justifies discontinuation of treatment.Decision by the study coordinator that MesoPher does not comply to quality requirements (advice of qualified person).Decision by the study coordinator that termination is in the patient’s best medical interest.Unrelated medical illness or complication.Serious logistical problems of practical problems in clean room.

### Objectives and analysis

#### Primary objective

Primary objective is to determine feasibility of using DCBI after CRS-HIPEC in patients with peritoneal mesothelioma. DCBI after CRS-HIPEC is deemed feasible when at least 75% of patients that are included in this trial complete the full treatment schedule. This cut-off is based on the fact that currently around 75% of patients undergoing CRS-HIPEC are fit to undergo adjuvant therapy, such as systemic chemotherapy.

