
### Statistical analysis

The statistical analyses/data summaries will be performed using SPSS. Other tools may be used for exploratory summaries and graphical presentations.

Primary endpoint is to determine the feasibility of administering DCBI after CRS-HIPEC in patients with malignant peritoneal mesothelioma. Based on previous results it is known that from all patients with colorectal carcinoma that underwent CRS-HIPEC, about 25% is not able to receive adjuvant systemic therapy due to postoperative complications. Feasibility is set if 15 of 20 patients (75%) were able to undergo leukapheresis successfully, production of PheraLys and dendritic cell vaccines was successful and when patients were able to complete the full adjuvant treatment schedule.

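### The 75% feasibility cut-off rests on the share of operated patients fit to start adjuvant therapy, but it is applied to all included patients completing leukapheresis, production and the full schedule

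*Protocol article*

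**What the plan says.** **The criterion.** Under Primary objective, DCBI after CRS-HIPEC is "deemed feasible when at least 75% of patients that are included in this trial complete the full treatment schedule". The registration table under Trial setting is similar: "DCBI therapy is considered feasible when 75% of patients enrolled in this study are able to receive and finish dendritic cell vaccination after CRS-HIPEC". Statistical analysis turns this into a count and adds components: "Feasibility is set if 15 of 20 patients (75%) were able to undergo leukapheresis successfully", production of the lysate and vaccines succeeded, and "when patients were able to complete the full adjuvant treatment schedule".

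**The schedule.** Patient timeline and additional procedures places leukapheresis before surgery and gives three biweekly vaccinations starting 8 to 10 weeks after it. Then: "At 3 and 6 months after the first vaccination, two additional booster vaccinations will be given". The full schedule is therefore five vaccinations.

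**The basis for 75%.** Primary objective says: "This cut-off is based on the fact that currently around 75% of patients undergoing CRS-HIPEC are fit to undergo adjuvant therapy". Statistical analysis names the source as patients with colorectal carcinoma who underwent CRS-HIPEC, of whom "about 25% is not able to receive adjuvant systemic therapy due to postoperative complications".

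**The concern.** The benchmark and the criterion measure different things.

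- **Numerator.** The benchmark counts patients fit to start adjuvant therapy. The criterion counts patients who finish five vaccinations.
- **Denominator.** The benchmark starts from patients who have had CRS-HIPEC. The criterion starts from inclusion, so failed leukapheresis, failed production and not reaching surgery all count against it.
- **Population and type of loss.** The benchmark comes from another disease, and the only loss it names is postoperative complications. The article's own list under Withdrawal of individual subjects foresees others: product not meeting quality requirements, clean-room problems, refusal, and change in condition.

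The article says that the cut-off is based on this benchmark, so the benchmark has to support it, and it does not. This is the only primary decision rule, and Introduction and Discussion link a phase III trial to a finding of feasibility. A therapy that matched the benchmark exactly at the point of starting could miss the cut-off through ordinary losses at steps the benchmark never counted.

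**Working it through.** **Inputs from the article**
- n = 20 and threshold 15 (Statistical analysis).
- Benchmark start rate s = 0.75 (Primary objective; Statistical analysis).
- Added steps: leukapheresis, production and release, reaching surgery, and completing three vaccinations and two boosters (Statistical analysis; Patient timeline and additional procedures).

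**Input not in the article (assumption)**
- q, the joint probability that a patient passes all added steps, given postoperative fitness or independently of it. It is varied below.

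**Step 1. Reproduce the stated figure.** 0.75 × 20 = 15, so the article's threshold is reproduced.

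**Step 2. Pass probability.** With p = s × q and X ~ Binomial(20, p), P(declared feasible) = P(X ≥ 15) = Σ C(20,k) p^k (1−p)^(20−k), summed over k = 15 to 20.

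| q (assumed) | p = 0.75 × q | Expected completers, 20 × p | P(X ≥ 15) |
|---|---|---|---|
| 1.00 | 0.750 | 15.0 | 61.7% |
| 0.98 | 0.735 | 14.7 | 55.6% |
| 0.95 | 0.7125 | 14.25 | 46.5% |
| 0.90 | 0.675 | 13.5 | 32.5% |
| 0.857 (three steps at 95%: 0.95³) | 0.643 | 12.9 | 22.5% |
| 0.80 | 0.600 | 12.0 | 12.6% |

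**Step 3. Break-even.** P(X ≥ 15) = 50% at p = 0.721. With s = 0.75 this means q = 0.721/0.75 = 0.96.

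**Step 4. Completion rate needed for a dependable pass.** P(X ≥ 15) reaches 80% at p ≈ 0.80 and 90% at p ≈ 0.83. Both exceed the benchmark before any added loss.

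**Step 5. Could a higher start rate make up for it?** Break-even needs s × q = 0.721. At q = 0.90, s must be 0.721/0.90 = 0.80. Illustrations (assumed):
- s = 0.85, q = 0.90: p = 0.765, pass probability 68%.
- s = 0.90, q = 0.90: p = 0.81, pass probability 84%.

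**The case against.** **75% may be meant as a target for the whole pathway.** Counting every included patient is the conservative choice for feasibility, and the Statistical analysis section evidently includes leukapheresis and production on purpose. That is a defensible endpoint. But the article does not present 75% as a free-standing target; it derives it from a start rate. The endpoint can stay, but the justification cannot.

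**DCBI may be easier to start than chemotherapy.** Introduction and Discussion describe it as causing little toxicity, so more than 75% might be fit for it, and Step 5 shows that this could offset the added losses. This stands as a limit on the size of the effect. It does not repair the rationale: the article claims no such offset, and it attributes the benchmark loss to postoperative complications, which also bear on fitness for DCBI at week 6.

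**Stronger readings that the article does not support**
- *DCBI that matches the benchmark would usually be declared infeasible.* At p = 0.75 the rule passes 62% of the time. The reverse needs q below about 0.96, and the article gives no value for q.
- *Recurrence would pull completion far below 75%.* One could feed the recurrence times cited in Introduction into the schedule, but nothing says that recurrence ends vaccination. Introduction has patients with incomplete cytoreduction still going on to DCBI, and withdrawal for a change in condition is left to judgement.
- *The survival criterion conflicts with the schedule.* The entry rule is "Expected survival prior to surgery must be at least 6 months", while the last booster falls about 34 to 36 weeks after surgery (8 to 10 plus 26 weeks). But the rule is an eligibility floor, not a forecast, and Introduction cites a median survival of 53 months after CRS-HIPEC. The two do not contradict each other.
- *Fewer than 15 successes would end development.* The article ties phase III to feasibility but does not say what follows a miss.

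**Conclusion.** The point stands as a mismatch between the cut-off and its stated basis, and it can be read directly from the text: fit to start versus completed, operated versus included. The benchmark's loss takes up the full 25% allowance, and the criterion then adds steps for which nothing is left.

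The size depends on a rate that the article does not give. With the start rate held at 75%, the pass probability is 62% if no added step ever fails, and 47%, 33% or 13% if those steps jointly succeed in 95%, 90% or 80%. Below about 96% joint success, an infeasible verdict is the likelier one. That is a mild condition across leukapheresis, manufacture, surgery and five vaccinations, but it is still an assumption, and a start rate above 75% would weaken or remove the effect.

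**What to change.** Make the cut-off and its basis like-for-like, in one of two ways.

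**(a) Align the criterion with the benchmark.** Apply 75% to patients who receive the first vaccination (numerator) among patients who underwent CRS-HIPEC (denominator). Vaccine starters must not become the denominator, because that would drop the postoperatively unfit patients whom the benchmark counts. State how an operated patient without a released product is handled; the benchmark has no such loss, so the comparable choice is to report those patients separately. The denominator may then be below 20, so the rule should be written as a proportion.

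**(b) Keep full-schedule completion among all included patients as primary.** Remove the justification by fitness for adjuvant therapy, derive the cut-off from a stated assumption for each step, and give the pass probability of the 15-of-20 rule under those assumptions.

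In either case, report leukapheresis success, product release, fitness at week 6, completion of the three biweekly vaccinations and each booster separately, with exact intervals and reasons for non-completion.

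**Cost.** An amendment to the wording of the primary endpoint. Ethics and dissemination reports three patients included at the time of writing, so the change would have come early. Under (a) the headline criterion is less demanding, and leukapheresis and production failures are reported beside the primary verdict instead of within it. Under (b) the team must commit to step rates it has not yet stated.
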